## Study investigational center(s)

A total of 3 centers are planned in 2 countries:

1. 2 sites in Lebanon
2. 1 site in Jordan

Each center is expected to enroll 12 eligible patients.

The Investigator sites/units should have immediate access to equipment and staff for resuscitation.

## Scientific committee / Data and safety monitoring board /

A scientific committee is in charge of the protocol design, the approval of the final protocol version and of the amendments, if any. The scientific committee will also discuss the results before writing all reports and publications.

A Data and Safety Monitoring Board (DSMB) will be constituted to ensure patient safety.

The DSMB is an expert committee, independent from the investigators and the sponsor of the clinical study, which periodically examines data accumulated during progress of the study and ensures that benefice/risk ratio remains acceptable for participating patients.

Primarily, the DSMB will approve the study protocol BIO-2017-0467 in order to confirm the study design and data safety monitoring plan.

The DSMB will independently make its recommendations for continuation, termination or modification of the conduct of the study.

The sponsor will timely provide the members of the DSMB with the safety data of the patients. In particular, a report will be sent to the DSMB members after the first stage is completed and 13 patients are accrued from all centers to decide about proceeding with the second stage of the study. By that time, they will provide the sponsor with written recommendations whether or not to proceed to the inclusion of the following patients and will give recommendations to change or not the methods of administration. An annual meeting will be held thereafter, andDSMB advices could be sought for any questions regarding the safety and well-being of the patients who will receive the study treatment.

The DSMB will include a board steering recommendations between the following experts, independent from any study involvement (apart from sponsor, subsidiaries or study team):

1. A physician, MD ([name]) specialist in gastrointestinal oncology at Institut Jules Bordet, Brussels, Belgium
2. A physician, MD ([name]) specialist in gastrointestinal oncology at Institut Jules Bordet, Brussels, Belgium
3. A physician, MD ([name]) specialist in gastrointestinal oncology at Memorial Sloan Kettering Cancer Center
4. A biostatistician ([name], PhD), Associate Professor of Medicine, and Director of the Biostatistics Unit at the Clinical Research Institute at the Faculty of Medicine, American University of Beirut (AUB)

All experts will necessarily have a prior clinical extended experience in immunotherapy in cancer and a significant involvement in clinical research and investigation development methods.

# DURATION AND DATES OF THE STUDY

The duration of this study depends on the results of the interim analysis, i.e., the probability of early termination, if only 2 or fewer patients achieve pCR at stage one (65.37% based on the study design). Interim analysis will be done on 13 patients once the surgery on the 13th patient is completed. The remaining patients will be enrolled based on the result of that analysis. The study duration is expected to be 4.5 years if the 2 stages of the study will be done. The first patient’s first visit is expected on 20 July 2018, and last patient last visit in on 02 May 2023. The 4.5-year duration includes 18 months of enrolment and 3 years of follow-up.

# STUDY POPULATION

## Number of patients

In this study, 44 patients with locally-advanced, potentially resectable rectal adenocarcinoma will be enrolled in total.

In this multicenter study, a mean number of 12 patients is expected to be enrolled by each center.

Since Simon’s two-stage design (Simon R, 1989) will be used:

1. 13 patients will be accrued in the first stage from all centers, until April 2019. If there are 2 or fewer patients with a pCR among these 13 patients, the study will be stopped.
2. Otherwise, 31 additional patients will be accrued for a total of 44.

The enrolment objectives for each center will take into consideration the enrolment period, i.e., 3 patients per month.

## Eligibility criteria

Before any study-related procedure is undertaken, written informed consent must be obtained (see Section 9.1.1).

For a patient to be eligible, all of the inclusion criteria and none of the exclusion criteria must be met.

### Inclusion criteria

For patient inclusion, all of the following criteria must be met:

1. Signed and dated informed consent form,
2. Patients aged ≥18 years.
3. Locally-advanced rectal cancer (cT2 N1-3, cT3 N0-3, evidence of extramural vascular or mesorectal fascia involvement).
4. <15 cm from anal verge
5. Histologically proven rectal adenocarcinoma.
6. ECOG performance score ≤ 1.
7. Have adequate organ function by meeting the following:
   - Absolute neutrophil count (ANC) ≥ 1.5 × 109/L;
   - Platelet count ≥ 100 × 109/L;
   - Hemoglobin ≥ 9 g/dL;
   - Total bilirubin level ≤ 1.5 × the upper limit of normal (ULN) range;
   - AST and ALT levels ≤ 2.5 × ULN or AST and ALT levels ≤ 5 x ULN (for subjects with documented metastatic disease to the liver);
   - Estimated creatinine clearance ≥ 30 mL/min according to the Cockcroft-Gault formula (or local institutional standard method).
8. Negative serum or urine pregnancy test at screening for women of childbearing potential who are sexually active.
9. Highly effective contraception for both male and female subjects throughout the study and for at least 30 days after last avelumab treatment administration if the risk of conception exists.

### Exclusion criteria

Patients will not be eligible for inclusion in this study if any of the following criteria is met:

1. Distant metastasis (M1).
2. Patients with T2 N0 or T4.
3. Recurrent rectal cancer.
4. Symptoms or history of peripheral neuropathy.
5. Prior radiotherapy or chemotherapy.
6. Current use of immunosuppressive medication, except for the following:
   - Intranasal, inhaled, topical steroids, or local steroid injection (e.g., intra-articular injection);
   - Systemic corticosteroids at physiologic doses ≤ 10 mg/day of prednisone or equivalent;
   - Steroids as premedication for hypersensitivity reactions (e.g., CT scan premedication).
7. Active autoimmune disease that might deteriorate when receiving an immuno-stimulatory agent. Patients with diabetes type I, vitiligo, psoriasis, or hypo- or hyperthyroid diseases not requiring immunosuppressive treatment are eligible.
8. Vaccination within 4 weeks of the first dose of avelumab and while on trials is prohibited except for administration of inactivated vaccines.
9. Active infection requiring systemic therapy.
10. Known history of testing positive for the human immunodeficiency virus or known acquired immunodeficiency syndrome.
11. Hepatitis B virus (HBV) or hepatitis C virus (HCV) infection at screening (positive HBV surface antigen or HCV RNA if anti-HCV antibody screening test positive).
12. Known prior severe hypersensitivity to investigational product or any component in its formulations, including known severe hypersensitivity reactions to monoclonal antibodies (NCI CTCAE v4.03 Grade ≥ 3).
13. Clinically significant (i.e., active) cardiovascular disease: cerebral vascular accident/stroke (< 6 months prior to enrollment), myocardial infarction (< 6 months prior to enrollment), unstable angina, congestive heart failure (≥ New York Heart Association Classification Class II), or serious cardiac arrhythmia requiring medication.
14. Persisting toxicity related to prior therapy (NCI CTCAE v. 4.03 Grade > 1); however, alopecia, sensory neuropathy Grade ≤ 2, or other Grade ≤ 2 not constituting a safety risk based on investigator’s judgment are acceptable.
15. Prior organ transplantation including allogenic stem-cell transplantation.
16. Other severe acute or chronic medical conditions including immune colitis, inflammatory bowel disease, immune pneumonitis, pulmonary fibrosis or psychiatric conditions including recent (within the past year) or active suicidal ideation or behavior; or laboratory abnormalities that may increase the risk associated with study participation or study treatment administration or may interfere with the interpretation of study results and, in the judgment of the investigator, would make the patient inappropriate for entry into this study.
17. Concurrent treatment with a non-permitted drug.
18. Patients suspected by the physician that he/she will not compliant to the protocol conduct.
19. Pregnant or breastfeeding patients.
20. Patient participating in another clinical trial.
21. Patient who is not willing to sign the consent form.
22. Any psychiatric condition that would prohibit the understanding or rendering of informed consent.
23. Legal incapacity or limited legal capacity patients receiving other oncology specific medication not authorized in the protocol.

## Duration of patient participation

For each patient, the participation will last 3 years.

The study planning is as follows:

1. Screening: no screening period
2. First-Patient In (FPI): 20 July 2018
3. First Patient First - Dose First Patient Last Dose: 10 weeks after first dose
4. First-Patient Last Visit: 3 years from FPI
5. Last-Patient In: 20 January 2020
6. Last Patient Last Visit: 02 May 2023
7. Follow-up: every 3 months after the surgery
8. Database lock: 02 June 2023
9. Key statistics: 20 July 2023
10. Clinical Study Report approved: 20 October 2023

## Discontinuation criteria / stopping rule(s)

The Investigator must document the reason of any patient withdrawal or discontinuation by a narrative description.

A patient may be discontinued from the study at any time for one or more of the following reasons:

1. Occurrence of an AE that, to the judgment of the Investigator or the Principal Investigator, may interfere with study conduct or study results
2. Protocol deviation that could invalidate the interpretation of the results
3. Lack of efficacy if relevant, to be defined on a “case by case” basis
4. Withdrawal of consent for any reason, at any time
5. Lost to follow-up
6. Administrative problems
7. Investigator decision in patient best interest
8. Pregnancy
9. Death

Data to be collected are detailed in Section 8.

The study can be stopped depending on the results of the interim analysis in this 2-stage study.

If a patient withdraws from the study or if the treatment is discontinued, the Investigator will make every effort to complete the final evaluation by performing an "end of study visit". All evaluation results, the date and a narrative description of the reason(s) for discontinuation must be recorded in the source documents and in the electronic Case Report Form (eCRF).

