# STUDY DESIGN

## Design

This is an open-label, single-arm multicenter and stage-2 phase II study investigating short-course radiation therapy (25 Gy in 5 fractions), followed 2 weeks later by 6 cycles of mFOLFOX-6 chemotherapy plus avelumab (10 mg/kg) given every 2 weeks in a successive manner such that mFOLFOX is administered 30 minutes after avelumab has been administered in patients with locally-advanced, potentially resectable rectal adenocarcinoma (**Figure 1**).

No screening period is planned.

All chemotherapy agents will be taken intravenously (infusion) every 2 weeks for 6 cycles during the treatment period (12 weeks), or until intolerable toxicity or withdrawal of patient’s informed consent. TME will performed 2 to 3 weeks after the last cycle of chemotherapy plus avelumab, depending on the patient’s condition and laboratory exams.

Each patient will be followed up for 3 years after surgery.

No reference therapy or placebo will be used in the trial.

Written informed consent must be obtained before any study specific medical procedure is performed.

Figure 1 Study design

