      - - Will be quantified in mm2 in the most abundant tumor-infiltrating area in both, the stroma and the tumor, of the D10 biopsy (continuous variable).
        - After the recruitment of around 5 patients, a cut-off value will be agreed upon and the numerical values corresponding to T cell infiltration (continuous variable) will then be classified as low or high or not applicable (categorical variable).
    - Microsatellite instability (MSI or MMR status):
      - - Will be evaluated once on either the baseline biopsy or D10 biopsy.
        - The MSI predictive markers to be assessed are: MLH-1, MSH-2, MSH-6, and PMS-2.
    - Image of the biopsy is to be provided.
    1. Concomitant medications
    2. Adverse event collection

### 8.2.3. Treatment period: visits 8 to 13

The procedures to be done from week 3 ± 3 days to week 13 ± 3 days (visits 8 to 14), starting D15 are as follows:

- - 1. Physical examination/vital signs/weight
    2. Laboratory tests:
    - Hematology assessments: CBC
    - Blood chemistry: BUN, creatinine, electrolytes, SGPT, SGOT, GGT, alkaline phosphatase, bilirubin
    - Urine or serum pregnancy test for women of childbearing potential who are sexually active
    - Free T4 and TSH
    1. Concomitant medications including mFOLFOX-6 chemotherapy protocol and anti-emetics:
    - Oxaliplatin 85 mg/m2 in a 2-hour infusion
    - Leucovorin 400 mg/m2 over 2 hours
    - 48-hour infusion of fluorouracil 2,400 mg/m2
    1. IMP administration: avelumab 10 mg/kg first administration at D15, then every 2 weeks for 6 cycles
    2. Adverse event collection
    3. Patient-reported outcome: quality of life assessment using FACT-C questionnaire

### 8.2.4. End of treatment visit including study completion and premature withdrawal: visit 13

Besides the procedures to be done at week 13 ± 3 days, tumor markers (CEA and CA 19-9) should be assessed at the end of treatment. Also, at the time patients discontinue the study treatment, a visit should be scheduled as soon as possible, but no later than 14 days from the last day of study medication, at which time all of the assessments listed for the End of Treatment visit will be performed. An End of Treatment eCRF page should be completed, giving the date and reason for stopping the study treatment.

### 8.2.5. Surgery: visit 14

Depending on the patient’s condition and laboratory exams, the procedures to be done 2 to 3 weeks ± 3 days after the last cycle of chemotherapy plus avelumab are as follows:

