### 8.2.7. End of study visit (last patient visit / last patient contact)

This visit and procedures also apply to patients who are prematurely withdrawn.

The last patient visit will be done at 3 years after the surgery, the visit procedures are as follows:

- - 1. Physical examination/vital signs/weight
    2. Laboratory tests:
    - Tumor markers (CEA and CA 19-9)
    1. Concomitant medications
    2. Adverse event collection
    3. Patient-reported outcome: quality of life assessment using FACT-C questionnaire
    4. Patient survival status
    5. Disease Status

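### Section 5.4 treats stopping study treatment like leaving the study, in conflict with Sections 3.1, 8.2.4 and 8.2.7; applied literally it can end follow-up early and make PFS censoring informative

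*Protocol*

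**What the plan says.** Section 5.4 lists reasons for which a patient may be discontinued from the study. They include "Occurrence of an AE that, to the judgment of the Investigator or the Principal Investigator, may interfere with study conduct or study results", a protocol deviation, and "Lack of efficacy if relevant", the last to be judged case by case. It then states: "If a patient withdraws from the study or if the treatment is discontinued, the Investigator will make every effort to complete the final evaluation". The means it names is an end of study visit, with the reason for discontinuation recorded. Withdrawal from the study and discontinuation of treatment share this one instruction.

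Three other places bear on the same patients:

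- **Section 8.2.4 (End of treatment visit):** "at the time patients discontinue the study treatment, a visit should be scheduled as soon as possible, but no later than 14 days" after the last study medication. At that visit "all of the assessments listed for the End of Treatment visit will be performed".
- **Section 8.2.7 (End of study visit):** the visit takes place 3 years after surgery. "This visit and procedures also apply to patients who are prematurely withdrawn".
- **Section 3.1 (Design):** treatment may end before six cycles because of intolerable toxicity, and "Each patient will be followed up for 3 years after surgery".

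On the endpoints, pCR is documented at the surgery visit (Section 8.2.5) and disease status every 3 months afterwards (Section 8.2.6). Section 12.8.2 analyses PFS in the ITT, MITT and PP sets and censors patients without an event at their last progression assessment. Section 12.4 defines the ITT set as all patients with at least one administration of avelumab.

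**The concern.** Stopping a drug and leaving a trial are different events, and only the second should end outcome collection. Section 5.4 merges them. A patient who stops during the chemotherapy period has not yet reached surgery or the three-monthly visits. If the end of study visit is that patient's final evaluation, no pathology result and no later disease status need be collected under that rule. The procedures listed in Section 8.2.7 include no pathology item.

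The situation will arise. Tables 2 and 3 require permanent discontinuation of avelumab for several toxicities. Section 5.4 does not say whether the treatment it means is avelumab alone or the whole regimen.

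What is at stake is mainly PFS in the ITT set. Early stoppers would be censored soon after they stop, and the reasons for stopping include adverse events and lack of efficacy. If these patients have a worse outlook than the others, Kaplan-Meier's assumption that censored patients resemble those still followed fails, and the estimate is too high. An SAP cannot repair this, because it cannot recover data that sites did not collect.

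**Working it through.** **Step 1. The sections side by side, for a patient who stops treatment and has not withdrawn.**

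| Section | Visit that applies | Follow-up afterwards |
| --- | --- | --- |
| 5.4 | End of study visit, as final evaluation | None implied |
| 8.2.4 | End of Treatment visit within 14 days | Not stated |
| 8.2.7 | None now; the end of study visit is at year 3, or earlier only on premature withdrawal | Implied to year 3 |
| 3.1 | Not stated | 3 years after surgery, every patient |

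Sections 5.4 and 8.2.4 name different visits for the same event. Sections 3.1 and 8.2.7 imply continued follow-up, while 5.4 implies its end. No section says outright that pathology, disease status and survival are still collected after treatment stops.

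**Step 2. The plan's own design figures, to see whether they are touched.** Inputs from Sections 4 and 12.2: stop at 2 or fewer pCR in 13; reject at 10 or more in 36; null rate 0.16; alternative 0.35. Exact two-stage binomial results:

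- early termination at 0.16: 0.6537 (the protocol states 65.37%);
- type I error: 0.0433 (within the stated 0.05);
- power at 0.35: 0.8008 (stated 0.8).

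All three agree with the protocol, and none depends on the wording of Section 5.4.

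**Step 3. Possible size of the PFS bias.** Inputs:

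- True overall 3-year PFS S = 50%. This is an assumed level, taken from the approximate 3-year DFS in Section 1.1.
- Fraction stopping early q = 10%, 18% or 25%. Assumed; the middle value matches the 8/44 = 18% enrolment allowance.
- Hazard ratio h of stoppers to continuers = 1 to 3. Assumed.
- Stoppers censored at t0 = 0.25 year; exponential times. Assumed.

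Formulas:

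1. Solve (1 − q)·exp(−3λ) + q·exp(−3hλ) = S for the continuers' hazard λ.
2. Survival up to censoring: S0 = (1 − q)·exp(−0.25λ) + q·exp(−0.25hλ).
3. Kaplan-Meier limit at 3 years: S0·exp(−2.75λ), because only continuers remain observed after t0.

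Example, q = 0.18 and h = 2: λ = 0.2025; S0 = 0.9422; exp(−2.75 × 0.2025) = 0.573; product 0.540. The estimate is 54.0% against a true 50%, a bias of +4.0 points.

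Bias in percentage points:

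| q | h = 1 | h = 1.5 | h = 2 | h = 3 |
| --- | --- | --- | --- | --- |
| 10% | 0.0 | 1.3 | 2.2 | 3.3 |
| 18% | 0.0 | 2.4 | 4.0 | 6.0 |
| 25% | 0.0 | 3.2 | 5.5 | 8.4 |

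If follow-up continues after treatment stops, this bias is zero in every cell.

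**The case against.** The strongest reply is that Section 5.4 never cancels surgery or follow-up. It refers to Section 8 for the data to be collected, and Section 8.2.4 has the specific rule for treatment stoppers. An End of Treatment visit now and an end of study visit at year 3 can coexist. The heading of 8.2.4 itself covers premature withdrawal, so much of the conflict may be loose naming of visits. This stands in part: the loss is something 5.4 can cause if followed literally, not something the protocol orders. It does not remove the problem, because 5.4 still names a different visit and calls it final, and no section says that collection continues.

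A reader might also infer more than the documents support:

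- **That power falls, for example to 73%.** The exact power with 33 evaluable patients is 0.730, but 33 of 44 means a 25% loss. Section 12.2 enrols 44 because 15 to 20% may not be evaluable. That loss leaves 44 × 0.85 = 37.4 to 44 × 0.80 = 35.2 patients, so about 35 to 37, with power of 0.78 to 0.82.
- **That the ITT PFS analysis cannot be done.** It can. The set and the censoring rule are defined; what may suffer is completeness and interpretation.
- **That 5.4 itself inflates pCR.** Unresected patients leave the primary analysis through the MITT definition in Section 12.4, whatever 5.4 says. A patient who stops early and is resected remains in MITT, provided the baseline assessment is available.
- **That some discontinuation criteria should be deleted.** That is debatable and would leave the adverse-event route in place. The statistical need is to keep collecting data, not to shorten the list.

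Finally, the stopping rate and the stoppers' prognosis are not in the documents, and with equal prognosis the bias is zero. That is right, and the range above starts at zero for that reason.

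**Conclusion.** The inconsistency is real and stands in the current text. Section 5.4 gives stopping treatment and leaving the study the same final visit, against Sections 3.1, 8.2.4 and 8.2.7. Applied literally, it can end the collection of pathology and disease-status data at the time treatment stops, and PFS censoring in the ITT set may then be informative.

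The illustrated upward bias in 3-year PFS is 0 to about 8 points. It rests on assumed stopping rates, hazard ratios, exponential times and censoring at about 3 months. The protocol neither confirms nor excludes any value in that range. The Simon design, the enrolment of 44 and the error rates are unaffected. The point should be corrected because the remedy is cheap and the data, once not collected, cannot be recovered; it does not invalidate the design.

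**What to change.** Reconcile Sections 3.1, 5.4, 8.2.4 and 8.2.7. In Section 5.4, say which treatment is meant and separate two cases:

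1. **Study treatment stopped, patient still in the study.** End of Treatment visit as in Section 8.2.4. Collection then continues: the pathology result if the patient is operated on, and three-monthly disease and survival status to year 3.
2. **Patient withdrawn from the study.** End of study visit as in Section 8.2.7. Where the reason is other than withdrawn consent, state that disease and survival status are still collected as far as consent allows.

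The list of reasons for discontinuation can stay as it is, and so can the withdrawal for pregnancy in Section 9.6. The change concerns data collection only and sets no rule for treatment or surgery. Its cost is a wording amendment and continued attendance at already scheduled visits for a few patients.
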